## Discussion

Preliminary analyses of the baseline characteristics of the study’s participants reveal.

that, thus far, a substantial portion of participants assigned to the intervention group did not receive the intervention as intended. Of the 216 women randomly assigned to the PTSC intervention, 103 received the intervention as designed (that is, they attended at least 8 of the 13 Sister Circles), while the remaining 113 did not. This indicates a need for culturally- and economically-sensitive mitigation strategies that will encourage higher receipt of the intervention. In an effort to uncover some of the factors related to low exposure to the PTSC program, we created a short survey to elicit information about why they were not participating. Two of the top 3 reasons cited for non-involvement in the study were related to the accessibility of the Sister Circles (transportation and scheduling), and the other reason was a matter of personal health (not feeling well enough to attend). These realities attest to the difficulties associated with designing and implementing a randomized trial in the real-world context of engaging with a socioeconomically vulnerable study population, whose members may be grappling with multiple comorbid conditions and various structural determinants of health. Additional analyses indicate that most of the attrition observed thus far occurred between the recruitment meeting and participants’ first Sister Circle session, despite the fact that participants meet their facilitator at the recruitment meeting, and facilitators contacted study participants in between the recruitment session and the first Sister Circle session. Bearing in mind that the reduced number of study participants exposed to the intervention threatens our ability to detect statistically significant differences between the intervention and usual care groups, and to tackle the issue of attrition prior to the first Sister Circle, we have shortened the time between the recruitment meeting and the first Sister Circle session to less than two weeks. This information informs our approach for the third cohort of participants. We will make the Sister Circle schedules more flexible, provide transportation assistance, and create protocols for facilitators to follow up with participants prior to the start of their Sister Circle. In addition, we will allow study participants assigned to the intervention to choose their Sister Circle from a menu of Sister Circles that vary by time, i.e., from a daytime, evening, and weekend Sister Circle.

Despite recruitment challenges, the PTSC-RCT joins a growing body of rigorously-evaluated community-based interventions geared toward reducing disparities in blood pressure control among AA women. They are typified by a blend of peer support and didactic training and education, the combination of which holds promise in addressing psychosocial and behavioral factors contributing to poorly controlled hypertension [8, 32–35]. These studies suggest that the cultivation of gender-specific, culturally concordant peer networks may shift underlying attitudes and beliefs about hypertension and its management, reinforce proper education about hypertension causes and treatment, and provide support and encouragement for adherence to antihypertensive regimens.

The overarching goal of the PTSC RCT is to determine if AA women with hypertension participating in the PTSC intervention exhibit improved blood pressure control; knowledge, attitudes, and beliefs about hypertension and its management; adherence to antihypertensive regimens; and psychosocial well-being; as well as reduced CVD risk factors and health care utilization stemming from CVD. We will also discern the program’s return on investment, an understudied area in the context of community-based interventions addressing disparities in cardiovascular disease. Indeed, the PTSC RCT presents an important opportunity to demonstrate the effectiveness of a longstanding community-based program emerging from the work and expertise of two AA women. There is indication to suggest that the conceptual underpinnings of the intervention, and its core elements, are associated with reductions in cardiovascular disease risk factors among AA women. Consequently, this study will illuminate the constellation of real-world barriers associated with designing and implementing randomized controlled trials among members of a highly vulnerable population, which is essential for identifying and advancing best-practices for reducing racial/ethnic disparities in cardiovascular health.

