### Power calculation

In order to detect a statistically significant difference in blood pressure control between the intervention and control groups post-exposure to the PTSC intervention, we need 440 participants (*n* = 220 per group) in our study. Our power calculations were based on the assumption of 80% HTN prevalence among study participants in both treatment arms at baseline, a two-sided alpha of 0.05, and a 15% reduction in the proportion of participants with high blood pressure after receipt of the PTSC intervention. The calculated sample size was 308, but our experience developing, implementing, and evaluating interventions with this target population suggests that we should anticipate a relatively high attrition rate. Thus, we computed a potential attrition rate of roughly 40%. In order to have sufficient power to detect a 15% reduction in HTN in the intervention group, we will recruit at least 40% above the estimated sample size, for a total sample size of 440 participants between Unity and BMSI health systems.

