### Analysis plan

Study data will be exported into Stata 15 for statistical analysis. We will set statistical significance at *p* ≤ 0.05. Baseline descriptive characteristics and outcomes will be analyzed using mean and standard deviation (SD) for continuous data, and counts and percentages for categorical data**.** We will conduct unequal variances t-tests in order to detect statistically significant differences between the treatment arms. To assess the impact of the PTSC program on participants’ blood pressure, weight, BMI, waist circumference, and all of the secondary outcomes, we will employ a difference-in-differences methodology to observe changes in participants’ outcomes at 3 months, 6 months, and 12 months post-intervention. We will also use multivariable regression analyses to discern whether or not participants’ outcomes improved as a result of receiving the PTSC intervention. Our models will control for patients’ sociodemographic characteristics (including age, marital status, and income), health insurance status, substance use (namely, smoking and drinking), and the presence of chronic conditions.

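### The sample size assumes a 15% reduction after receipt and allows only for attrition, but 48% of assigned women received the program; power as randomised should be restated, and the regression exposure fixed as assigned arm

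*Protocol article*

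**What the plan says.** The Power calculation takes as its effect "a 15% reduction in the proportion of participants with high blood pressure after receipt of the PTSC intervention". Its other inputs are an 80% starting prevalence of hypertension in each arm and a two-sided 5% significance level. The same section later words the 15% as a reduction in the intervention group. It states "The calculated sample size was 308", then "we computed a potential attrition rate of roughly 40" per cent, and arrives at 440 women, 220 per group. Target power is not stated.

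The Discussion reports uptake so far: "Of the 216 women randomly assigned to the PTSC intervention, 103 received the intervention as designed", defined as attending at least 8 of the 13 sessions. The other 113 did not. Two of the three leading reasons for non-involvement were scheduling and transportation. On the third the section says: "the other reason was a matter of personal health (not feeling well enough to attend"). It acknowledges that low exposure threatens the ability to detect a difference between the groups, and lists access measures for the third cohort. It gives no revised power or sample size.

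The Hypotheses section compares patients randomised to PTSC with patients receiving usual care. The Analysis plan describes a comparison between arms and difference-in-differences, and adds multivariable regression to find out whether "outcomes improved as a result of receiving the PTSC intervention". The abbreviation list contains ITT, but the text shown does not use it.

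**The concern.** Attrition and non-receipt are different problems. Attrition reduces the number of women analysed and, in the simple calculation, leaves the effect unchanged. Non-receipt leaves the number unchanged and shrinks the average difference between the arms as randomised. An attrition allowance therefore does not cover non-receipt. The Discussion blurs the two: it reports non-receipt of the program, then calls the loss before the first session attrition.

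Two things are at stake. First, if the 15 points are the effect in women who attend, the 440 women give much less power for the randomised comparison than the Power calculation conveys, and a null result would say little about whether the program works. Second, the word receiving in the Analysis plan leaves room for an analysis by attendance. Feeling too unwell to attend was one of the leading reasons for not taking part, so attenders and non-attenders may differ in health. Adjustment for chronic conditions cannot be assumed to capture that.

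**Working it through.** **Inputs.** From the Power calculation: 80% with high blood pressure at baseline, taken as the control proportion; two-sided alpha 0.05; 15% reduction; 308 before attrition; 40% attrition; 440 in total, 220 per group. From the Discussion: 103 of 216 received the program. Assumptions of this check: 80% target power, 1:1 analysis, and a two-proportion z-test on the follow-up proportion.

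**1. The plan's own figure.** With p1 = 0.80, p2 = 0.65 and mean m = (p1 + p2)/2,

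n per arm = [1.96·√(2m(1−m)) + z(power)·√(p1(1−p1) + p2(1−p2))]² / (p1−p2)².

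- 80% power: 138 per arm, 276 in total; with continuity correction 151 per arm, 302 in total.
- 85% power: 158 per arm, 316 in total; unpooled variance 310.

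The stated 308 lies within 3% of 302, 310 and 316. Read as a relative reduction (0.80 v 0.68), the total at 80% power is 418 to 450, which does not match. The planned effect is therefore taken as 15 percentage points.

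**2. Receipt and dilution.** Receipt = 103/216 = 0.477. If women below 8 sessions gain nothing, the as-randomised difference is 0.15 × 0.477 = 0.0715, that is 0.80 v 0.728.

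**3. Power.** Power = Φ[(d − 1.96·SE0)/SE1], with SE0 = √(2m(1−m)/n) and SE1 = √((p1(1−p1) + p2(1−p2))/n).

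At n = 220: SE0 = 0.0405 and SE1 = 0.0403, so (0.0715 − 0.0793)/0.0403 = −0.19 and power is 42%.
At n = 132 (440 × 0.6 / 2): SE0 = 0.0523 and SE1 = 0.0521, so (0.0715 − 0.1024)/0.0521 = −0.59 and power is 28%.

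| Effective receipt | Difference (points) | 132 per arm | 154 per arm | 220 per arm |
|---|---|---|---|---|
| 100% | 15.0 | 78% | 84% | 94% |
| 47.7% (observed, no benefit below 8 sessions) | 7.2 | 28% | 32% | 42% |
| 57.5% (all of an assumed 50 Baltimore intervention women receive it: (103 + 50)/266) | 8.6 | 37% | 42% | 56% |
| 60.8% (non-receivers get a quarter of the effect) | 9.1 | 41% | 46% | 60% |
| 73.8% (non-receivers get half) | 11.1 | 54% | 61% | 76% |
| 75% | 11.3 | 55% | 62% | 77% |

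At the diluted 7.2 points, 80% power needs 552 analysed per arm, 1,104 in total, against 276 for 15 points by the same formula. At 220 per arm with no attrition, 80% power needs about 78% effective receipt; at 154 per arm about 94%; at 132 per arm even full receipt gives only 78%.

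**4. Overlap of attrition and non-receipt.** The 28% treats the two as independent. At the other extreme, every intervention woman lost is a non-receiver; receipt among those analysed is then 0.477/0.6 = 79%, and power at 132 per arm is about 60%, in a sample that is no longer the randomised one.

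**5. What the regression estimates.** The Hypotheses refer to women randomised to PTSC. The Analysis plan's regression refers to receiving PTSC. The Discussion defines receipt by attendance, but no analysis text uses that definition as an exposure variable. The wording thus admits two exposures, assigned arm and attendance, and only the first is protected by randomisation.

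**The case against.** **The 15% may already be an arm-level target.** The Power calculation also speaks of a reduction in the intervention group and of a difference between the groups, and does not say where the 15% comes from. On that reading, multiplying by 0.477 discounts a figure that was never per receiver. This stands as a limit: the dilution figures are conditional. It does not remove the point, because an arm-level 15 points at 48% receipt would require about 31 points (15/0.477) in receivers if non-receivers gain nothing, and the plan does not say so.

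**A reader might infer that power simply is 28-42%.** The documents do not support that without conditions. It needs no benefit below 8 sessions, unchanged uptake in the third cohort despite the planned access measures, and attrition independent of receipt. It also concerns a two-proportion test, whereas difference-in-differences and adjusted regression are planned; power for those was not computed.

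**A reader might infer that the plan specifies an as-treated analysis.** It does not. That reading rests on one word in the Analysis plan, against hypotheses worded by randomised group and a comparison between arms. Follow-up payments are tied to data collection sessions, not to attendance at the circles. An article may leave analysis populations to a fuller document, and ITT in the abbreviation list may belong to a figure not shown. What stands is the inconsistent wording.

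**Bias toward benefit is not demonstrated.** Two of the three leading reasons were logistical, and difference-in-differences removes stable baseline differences. Confounding by health remains plausible, likely in the direction of benefit, but neither its direction nor its size can be established from the document.

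**The authors acknowledge the threat.** They do, with mitigation, but without a figure.

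**Conclusion.** The point holds in conditional form and should be fixed. If the 15 points are the effect in receivers and non-receivers gain nothing, the as-randomised difference is about 7.2 points and power is about 28% to 42% at 132 to 220 per group. With effective receipt of 57-75%, through partial benefit or better uptake, it is about 37% to 77%. All of these are below 80%, so the statement that 440 women give sufficient power is not supported for the randomised comparison on a per-receiver reading. The attrition allowance does not repair this, and the acknowledged loss is left unquantified.

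The wording of the regression is a clarification, not evidence of a planned biased analysis. Only if receipt were used as the exposure would the protection of randomisation be lost.

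**What to change.** 1. In the Analysis plan, define the exposure in the primary blood pressure analysis and in the regression as assigned arm. State that all randomised women, including the 113 who did not receive the program as designed, stay in outcome follow-up and analysis whatever their attendance.
2. In the Power calculation, say whether the 15 points are per receiver or per arm, and state the target power. Restate power under the observed 48% receipt, with the assumptions on benefit below 8 sessions and third-cohort uptake, as a range. Say that the attrition allowance does not cover non-receipt.
3. Optionally, add a secondary complier-average estimate with random assignment as the instrument. Number of sessions is preferable to the 8-session cut as the exposure, because the cut assumes no benefit below it.

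Cost: changes of wording, a restated and less favourable power figure, and one secondary analysis if adopted. No extra patients. Recruitment of the Baltimore participants still lies ahead in the document, so the change can be made before their data are collected.

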## Data Availability

The datasets used and/or analyzed during the current study are available from the corresponding author on reasonable request.

## Abbreviations

AA: African American
AIR: American Institutes for Research
BMI: Body mass index
BMSI: Baltimore Medical System, Incorporated
CVD: Cardiovascular disease
FQHC: Federally Qualified Health Center
GED: General Educational Development
GPHIC: Gaston and Porter Health Improvement Center, Inc.
ITT: Intent-to-treat
JHCHDS: Johns Hopkins Center for Health Disparities Solutions
PTSC: Prime Time Sister Circle
RCT: Randomized controlled trial
